### ***Adaptive MAD Cohorts in Part C***

Based on safety and available PK and/or PD data from cohorts in Part A and Part B (if applicable), TLC-2716 doses for Part C may be chosen up to a total daily dose of 50 mg. If the total daily dose in any cohort in Part C is greater than has been evaluated in any prior cohort, then sentinel dosing including one subject randomized to placebo and one subject randomized to TLC-2716 will be completed. Randomization of the remaining eight subjects in the cohort will be determined based on evaluation of all safety and tolerability data through Day 2 for these two sentinel subjects. Additionally, if doses chosen in two or more adaptive cohorts exceed the dose evaluated in a previous cohort, those cohorts will be conducted in a staggered manner (lowest dose first), with the same stopping rules applied. Part C cohorts may be initiated in parallel with cohorts in Part B if the total daily dose under evaluation is at or below a dose already evaluated.

The sponsor, in consultation with the investigator, may choose not to initiate any or all adaptive cohorts if deemed unnecessary.

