### **Part C (SAD and/or MAD), Adaptive Cohorts 11-15**

Based on available safety, PK, and/or PD data from Part A and Part B (if applicable), doses for Part C (optional, adaptive Cohorts 11-15) will be chosen up to a total daily dose of 50 mg. The frequency of dosing (QD or twice daily [BID]), duration of dosing (single on one day or multiple over 14 days), and fasting versus fed status may also be modified versus Parts A and B. If dosing is administered in the fed state, standard meal conditions may also be modified at sponsor discretion. QD doses will be administered in the morning following a standard meal, and BID doses will be administered after a standard morning meal and evening snack, with the second dose administered 12 hours ( $\pm$  10 minutes) after the morning dose. Once determined, dose level, duration of dosing, frequency of dosing, and meal conditions will remain consistent within a cohort. For any multiple-dose cohort in Part C with BID dosing, both morning and evening doses must be administered on Day 14.

Within each cohort, 10 unique subjects will be randomized 4:1 to receive up to a total daily dose of 50 mg TLC-2716 (N = 8) or PTM (N = 2) for either 1 day (as in Part A) or 14 days (as in Part B). Adaptive, multiple-dose cohorts in Part C may be initiated in parallel with previous cohorts if the total daily dose under evaluation is at or below a dose already evaluated in Part B. If doses chosen in 2 or more adaptive cohorts exceed the dose evaluated in a previous cohort in Part B, these cohorts will be conducted in a staggered manner (lowest dose first), with the same stopping criteria as detailed in Section 3.3. Additionally, if the total daily dose in any cohort in Part C is greater than has been evaluated in any prior cohort, then sentinel dosing including one subject randomized to placebo and one subject to TLC-2716 will be included. Randomization of the remaining eight subjects in the cohort will be based on evaluation of all safety and tolerability data through Day 2 for these two sentinel subjects.

The sponsor, in consultation with the investigator, may choose not to initiate any or all adaptive cohorts if deemed unnecessary.

The cohorts and study treatments for Part C are as follows:

| Cohort | Day -1a   | Single Dose (Day 1) or Multiple Doses (Days 1-14)                                 |

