Within Part A and SAD cohorts in Part C, initiation of single-dose administration at escalating dose levels will be determined by evaluation of cumulative safety data, and available and relevant PK and PD data up to and including Day 4, following single-dose administration of the previous dosing cohort. Similarly, in MAD cohorts in Parts B and C, initiation of multiple-dose administration at a higher dose level will be determined by evaluation of safety and available PK and PD data from all subjects enrolled through Day 14 of the previous dosing cohort. Additionally, in adaptive cohorts in Part C, sentinel dosing will be utilized in any cohort wherein the total daily dose to be administered is greater than has previously been evaluated. In these multiple-dose cohorts, to support a comprehensive evaluation of the relationship between TLC-2716 PK and PD, all subjects regardless of treatment assignment will be administered placebo capsule(s) on Day -1 to characterize the baseline daily variation of PD markers for subsequent comparison with changes that occur during dosing of TLC-2716 or PTM from Day 1 through 14. Additional details regarding dose escalation criteria are provided in Section 3.2.

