### 1.3.2. Rationale for Dose Selection

In this FIH study, oral doses of TLC-2716 ranging from 0.5 mg to a maximum of 50 mg per day (a 100-fold dose range) will be evaluated in healthy subjects. These doses were selected to provide predominantly liver exposure and minimize the potential for adverse effects mediated by systemic exposure (e.g., impact on reverse cholesterol transport). A starting dose of 0.5 mg and a maximum dose of 50 mg provide 672- and 6.7-fold safety margins based on the NOAEL observed in the 4-week GLP toxicity study in monkeys, the most sensitive preclinical species evaluated (Table 1). Based on pre-clinical pharmacology data, it is expected that doses at the lower end of this range will demonstrate efficacy for relevant clinical parameters based on the preferential liver distribution of TLC-2716. For example, in the DIO mouse and HFD-fed ZDF rat models, a daily TLC-2716 dose of 1 mg/kg administered for 2-3 weeks led to significant reductions in liver TG, plasma TG, and cholesterol concentrations. Based on allometric scaling for mice and rats, this dose is equivalent to a human equivalent dose (HED) of approximately 6 to 11 mg per day in a 70-kg human.

**Table 1. Estimated Dose Margins Following Oral Administration of TLC-2716 Based on 4-week, GLP Chronic Toxicology Studies**

| Species | Duration of Dosing (Days) | NOAEL (mg/kg/day) | AUC 0-24 (ng.h/mL)    | Human Equivalent NOAEL (mg) a | Dose Margins b |       |       |
|---------|---------------------------|-------------------|----------------------------------|------------------------------------------|---------------------------|-------|-------|
|         |                           |                   |                                  |                                          | 0.5 mg                    | 20 mg | 50 mg |
| Mouse   | 28                        | 80                | 149.13 (male)
162.11 (female) | 455                                      | 910                       | 22.8  | 9.1   |
| Monkey  | 28                        | 15                | 51.08 (male)
74.09 (female)   | 336                                      | 672                       | 16.8  | 6.7   |

AUC0-24 = area under the plasma concentration-time curve from time 0 to 24 hours concentration; FIH = first-in-human; HED = human equivalent dose; NOAEL = no-observed-adverse-effect-level

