### 3.1.2. Part B: Multiple-Ascending Dose [MAD] (Cohorts 6-10)

Part B will evaluate the safety, tolerability, PK, and PD of multiple-ascending doses of oral TLC-2716 or placebo under fed conditions. Part B will proceed in up to 5 dose-escalation cohorts and will be governed by a review of safety, tolerability, and any available and relevant PK and/or PD data, and study-specific stopping criteria. Planned study treatments within each cohort are provided in [Table 3](#).

- Randomized, blinded (sponsor-unblinded), placebo-controlled, multiple-ascending doses of TLC-2716 in healthy subjects. An attempt will be made to enroll at least 3 subjects in each cohort with Screening TG ≥ 150 mg/dL and/or low-density lipoprotein cholesterol (LDL-C) ≥ 130 mg/dL.
- Within each cohort, 10 unique subjects will be randomized 4:1 to receive either blinded TLC-2716 (N = 8) or PTM (N = 2) QD for 14 days.
- Part B (Cohort 6) may be initiated after the evaluation of cumulative safety, tolerability, and any relevant and available PK and/or PD data from all subjects enrolled in Cohort 3 in Part A (up to and including Day 4).

- For Cohorts 7-10, dosing may be initiated after evaluation of cumulative safety, tolerability, and any relevant and available PK and/or PD data from all subjects enrolled in the previous cohort in Part B through Day 14.
- All study drugs in Part B will be administered in the morning following a standard meal.

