### ***MAD Cohorts in Part B***

Dosing in Cohort 3 of the SAD portion of the study (Part A) will be completed prior to proceeding with the MAD portion of the study. Initiation of multiple dosing within Cohort 6 will be determined by a review of the cumulative safety, and any relevant and available PK and/or PD data through Day 4 of Cohort 3 in Part A.

Initiation of subsequent multiple-dose cohorts at a higher dose will be determined upon evaluation of all safety data, and any relevant and available PK and/or PD data through Day 14 from all subjects enrolled in the previous multiple-dose cohort.

In both Parts A and B, escalation to a dose higher than previously studied may occur only in the absence of dose-limiting toxicity and/or not meeting any prespecified stopping criteria.

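### Section 3.2 does not tie the Part C parallel-start rule to doses evaluated in Part B, so read alone it lets a single Part A dose open a 14-day cohort without sentinels

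*Combined protocol and SAP*

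**What the plan says.** The protocol and SAP state the rule for starting Part C cohorts in parallel four times.

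- **Protocol Section 3.2, Adaptive MAD Cohorts in Part C.** Part C cohorts may start in parallel with "cohorts in Part B if the total daily dose under evaluation is at or below a dose already evaluated". The sentence ends there. Part B identifies the cohorts running alongside; it does not say where the reference dose was given.
- **Protocol synopsis (Part C), protocol Section 3.1.3 and SAP 1.2.3.** Multiple-dose adaptive cohorts may start in parallel "if the total daily dose under evaluation is at or below a dose already evaluated in Part B".

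Three other provisions bear on the point.

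- **Sentinels (Section 3.2, same paragraph).** "If the total daily dose in any cohort in Part C is greater than has been evaluated in any prior cohort, then sentinel dosing" is required, with one active and one placebo subject assessed through Day 2.
- **Day 14 review.** Section 1.3.1 says that "in MAD cohorts in Parts B and C, initiation of multiple-dose administration at a higher dose level will be determined by evaluation of safety". That review also takes in PK and PD results where they exist, and must reach Day 14 for every subject of the preceding cohort. Section 3.2 itself states this review only under its Part B heading: "Initiation of subsequent multiple-dose cohorts at a higher dose will be determined upon evaluation of all safety data", with data through Day 14 of the previous multiple-dose cohort.
- **Timing of Part B.** "Part B (Cohort 6) may be initiated after the evaluation of cumulative safety, tolerability" and other available data from Cohort 3 through Day 4 (Section 3.1.2). Part A therefore runs ahead of Part B by design.

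**The concern.** The two wordings set different gates. Under the stricter one, a 14-day adaptive cohort running alongside Part B can only use a dose that has already been given repeatedly to an earlier cohort. Under the Section 3.2 wording, one administration of that dose in Part A is enough.

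If Section 3.2 were applied alone, eight active subjects could begin 14 days at a dose supported in humans only by single-dose data, while Part B was still at a lower dose. Nothing else in that section would stop it. Section 3.2 is also where Sections 1.3.1 and 8.2.1 send the reader for the escalation criteria, and no text says which wording prevails.

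**Working it through.** The plan gives no figure of its own here, so the check compares the wordings and then applies each to the planned doses.

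**Does anything in Section 3.2 close the gap?**

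1. *Parallel-start sentence.* The reference dose carries no part. A Part A single dose satisfies it literally.
2. *Sentinel trigger.* It requires a dose above that of any prior cohort. A Part A cohort is a prior cohort, so a dose equal to one given in Part A does not trigger it.
3. *Stagger sentence.* It needs two or more adaptive cohorts, so it does not stop a single one.
4. *Day 14 review.* It appears under the Part B heading only. The extension to Part C is in Section 1.3.1.

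**Inputs.** Planned single doses in Part A (Table 2) and planned daily doses in Part B (Table 3) are both 0.5, 2, 6, 12 and 20 mg. Cohort 6 opens only after Cohort 3 (6 mg single dose) has been reviewed. The human-equivalent NOAEL from the 28-day monkey study is 336 mg (Table 1).

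**Ceiling for a parallel 14-day Part C cohort (mg/day).** Section 3.2 read alone gives the highest Part A dose evaluated. The other three texts give the highest Part B dose evaluated. The ratio is the first divided by the second.

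| Highest Part A dose evaluated | Highest Part B dose evaluated | Section 3.2 alone | Other three texts | Ratio |
|---|---|---|---|---|
| 6 | none | 6 | none | – |
| 6 | 0.5 | 6 | 0.5 | 6/0.5 = 12 |
| 12 | 0.5 | 12 | 0.5 | 12/0.5 = 24 |
| 20 | 0.5 | 20 | 0.5 | 20/0.5 = 40 |
| 20 | 2 | 20 | 2 | 20/2 = 10 |
| 20 | 6 | 20 | 6 | 20/6 = 3.3 |
| 20 | 12 | 20 | 12 | 20/12 = 1.7 |
| 20 | 20 | 20 | 20 | 1 |

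The sentinel rule is triggered in none of these rows.

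**Comparison with planned steps in Part B.** 2/0.5 = 4; 6/2 = 3; 12/6 = 2; 20/12 = 1.7. The largest is 4-fold.

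**Bound from the nonclinical data.** Section 1.3.2 states: "A starting dose of 0.5 mg and a maximum dose of 50 mg provide 672- and 6.7-fold safety margins based on the NOAEL" in monkeys. On the same basis, 336/6 = 56, 336/12 = 28 and 336/20 = 16.8; the last agrees with Table 1. Every dose in the table above therefore stays within the stated nonclinical cover.

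**The case against.** The strongest reply is that Section 3.2 is ambiguous rather than permissive. Its sentence names Part B and sits under a heading about multiple-dose cohorts, so a reader could take the reference dose to be one evaluated in those Part B cohorts. Three parallel texts say exactly that, a dose that satisfies them also satisfies Section 3.2, and Section 9.1.10 requires the protocol to be followed. Section 1.3.1 requires Day 14 review for Parts B and C, and Sections 3.1, 3.1.3 and 8.2.1 make progression depend on data review. The sponsor, not site staff, designs and initiates adaptive cohorts, in consultation with the investigator. Part B has no sentinels either, so their absence at a previously tested dose is normal for this design. On this view the 12- to 40-fold figures describe one sentence in isolation.

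Much of that stands: misuse is unlikely, and the figures are a literal ceiling rather than an expected course. It does not make the text consistent. Each version is a permission, and none is said to govern. Sections 1.3.1 and 8.2.1 both refer back to Section 3.2, and the general review requirements do not name a reference dose. The sentinel point also cuts the other way. Because Part B has no sentinels, Day 14 review of the lower repeated dose is the main safeguard between multiple-dose cohorts, and that is the step the literal sentence bypasses.

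A further objection is that limiting the sentence to multiple-dose cohorts would remove a parallel-start option for single-dose Part C cohorts. This fails. The sentence already sits under the adaptive MAD heading, and the other three texts also confine the rule to multiple-dose cohorts.

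**Conclusion.** The concern holds. Section 3.2 is looser than the three other statements of the same rule, and its sentinel trigger does not compensate. After Cohort 6 has been evaluated, the literal ceiling exceeds the intended one by at least 12-fold, and by 40-fold if Part A is complete. With Part A complete, the excess shrinks as Part B advances and disappears after Cohort 10.

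These ratios assume that planned doses are unchanged, that a dose given once and reviewed counts as evaluated, and that Section 3.2 is applied without the other texts. What is at risk is a skipped repeat-dose review in humans, not a dose outside the nonclinical margins. This is an inconsistency in one section, not a gap across the whole protocol. It should be fixed because it concerns a dosing gate in a first-in-human study.

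**What to change.** Change one sentence in Section 3.2. Limit it to multiple-dose Part C cohorts and end it with the condition used elsewhere: "if the total daily dose under evaluation is at or below a dose already evaluated in Part B". The ceiling for a parallel 14-day cohort then equals the highest dose evaluated in Part B; with Part A complete and only Cohort 6 evaluated, it falls from 20 to 0.5 mg/day.

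Leave the stagger sentence in Section 3.2 as it is. It also omits the Part B qualifier, but there the omission is not shown to loosen the rule, and narrowing it could reduce protection.

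The synopsis, Section 3.1.3 and SAP 1.2.3 need no change. The edit requires no extra subjects or procedures and gives up no flexibility that those three texts allow.

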## **3.3. Protocol-Specific Stopping Criteria**

### **3.3.1. Subject Study Drug Discontinuation Criteria**

The severity of AEs will be graded using the Common Terminology Criteria for Adverse Events version 5.0 (CTCAE v5.0) ([Appendix 4](#)).

Study drug must be discontinued in subjects who experience any of the following:

- A confirmed, treatment-emergent, treatment-related, serious AE (SAE) or  $\geq$  Grade 3 AE
- Any  $\geq$  Grade 3 clinically significant laboratory abnormality (confirmed by repeat testing) as defined by the Common Terminology Criteria for Adverse Events (CTCAE) v5.0 for Severity of Adverse Events and Laboratory Abnormalities
- Symptoms of drug-related hepatotoxicity, and/or ALT or AST  $> 5 \times$  ULN, or ALT  $> 3 \times$  ULN and total bilirubin  $> 2 \times$  ULN or INR  $> 1.5$ , confirmed by immediate repeat testing

Study drug and/or study procedures may also be discontinued in the following instances:

- Intercurrent illness that would, in the judgment of the investigator, affect assessments of clinical status to a significant degree
- Unacceptable toxicity, as defined in the toxicity management section of the protocol, or toxicity that, in the judgment of the investigator, compromises the ability to continue study-specific procedures or is considered not to be in the subject's best interest
- Subject request to discontinue for any reason
- Subject noncompliance
- Pregnancy during the study (Refer to [Appendix 3](#))
- Investigator discretion
- Discontinuation of the study at the request of TLC, regulatory agency, or an Institutional Review Board (IRB)/Independent Ethics Committee (IEC)

### **3.3.2. Study-Specific Stopping Criteria**

Dose escalation or study drug dosing of a cohort will be suspended and based on a full review of the clinical data by the TLC medical monitor (MM) or designee, and in discussion with the investigator, may be halted when:

- 1 subject dosed with TLC-2716 experiences a treatment-emergent SAE deemed possibly related to study drug in the opinion of the investigator
- 2 subjects dosed with TLC-2716 within 1 cohort experience elevations in liver biochemistry tests of ALT and/or AST  $> 5 \times$  the ULN, or ALT  $> 3 \times$  ULN and total bilirubin  $> 2 \times$  ULN or INR  $> 1.5$ , confirmed by immediate repeat testing
- 2 or more subjects dosed with TLC-2716 experience the same  $\geq$  Grade 3 AE deemed possibly related to the study drug in the opinion of the investigator
- 2 or more subjects dosed with TLC-2716 experience a clinically significant  $\geq$  Grade 3 laboratory abnormality of similar nature (confirmed on repeat testing) and possibly related to the study drug in the opinion of the investigator
- The number and/or severity of AEs justify study discontinuation
- The sponsor requests study discontinuation

Decisions to reinstate the study will be made in consultation with the sponsor and pending a comprehensive safety review.

### **3.4. Duration of Dosing**

The duration of dosing for each part will be as follows:

Part A (SAD): 1 day

Part B (MAD): 15 days (including PTM dosing for all subjects on Day -1)

Part C (Adaptive SAD and/or MAD): 1 or 15 days (including PTM dosing for all multiple-dose subjects on Day -1)

### **3.5. Clinic Confinement**

Following Screening and admission procedures, eligible subjects will be confined to the study center beginning at admission (Day -1 for SAD cohorts; Day -2 for MAD cohorts) until the completion of assessments on Day 4 (SAD cohorts), or Day 17 (MAD cohorts).

Subjects will return  $14 \pm 2$  days after the last dose for an in-clinic follow-up visit (i.e., Day 15 [ $\pm 2$  days] for SAD cohorts; Day 28 [ $\pm 2$  days] for MAD cohorts).

### **3.6. Pharmacokinetic Assessments**

PK assessments will occur on assigned study days and time points as outlined in [Table 5](#) and [Table 6](#), and [Section 6.5](#).

Plasma concentrations of TLC-2716 (and its metabolites, as applicable) will be determined and PK evaluated. PK parameters will be estimated, as appropriate. Plasma concentrations of other metabolites may also be determined and PK explored.

### **3.7. Pharmacodynamic Assessments**

Blood samples and stool samples for assessment of PD biomarkers related to TLC-2716 and its mechanism of action will be collected throughout the study as outlined in [Table 5](#) and [Table 6](#), and [Section 6.6](#).

### **3.8. Biomarker Sample for Optional Genomic Research**

In addition to the study-specific informed consent to be signed by each subject participating in the study, subjects will be required to document an agreement to provide additional samples for optional genomic research. From subjects who agree to participate and provide their additional specific consent, a separate blood specimen will be collected to isolate DNA for genomic testing. This specimen will be used to study genetic and genomic mechanisms that may contribute to underlying metabolic diseases and outcomes. Stored specimens may also be used to evaluate the association of genetic and genomic markers with study drug response, including metabolism and/or AEs, and to determine future treatment predictions for TLC-2716 and/or other approved or exploratory medications. This sample should be collected on Day -1 prior to dosing but may be collected at any time during the study, if necessary.

The specimen collected for optional genomic research will be destroyed no later than 15 years after the end of the study or per country requirements.

### **3.9. Safety Assessments**

Safety assessments will be performed throughout the study as outlined in [Table 5](#), [Table 6](#), and [Section 6.7](#).

### **3.10. End of Study**

The end of this study will be the last subject's last observation (or visit).

## **4. SUBJECT POPULATION**

### **4.1. Number of Subjects and Subject Selection**

A total of up to 150 unique subjects will be enrolled in the study, with an approximately even distribution of healthy male and non-pregnant, non-lactating female subjects, 18 to 55 years of age, inclusive, at Screening.

#### **4.1.1. Subject Replacement**

If necessary, replacement subjects may be enrolled after discussion and approval from the TLC MM, or designee, if subjects do not complete all PK procedures or the subject is considered non-evaluable. Replacement subjects will not be enrolled for subjects who discontinue the study due to study drug-related AEs.

